#### Management of screen positive women

Individuals who have any of the Group 1a-c HPV types detected (figure 3) will be offered visual assessment for treatment (VAT) at local health facilities (PHCs or district hospital in Mizoram, or the study organisations’ secondary hospitals in Tamil Nadu). VAT involves examination for eligibility for treatment using 3%–5% acetic acid application. Thermocoagulation will be used to treat screen positive women who are eligible, based on the following criteria:^30^

The transformation zone (TZ) is fully visible, any lesion is wholly visible and not suspicious for cancer, and does not extend into the endocervix, or the lesion does not occupy more than 75% (3 quadrants) of the TZ.The woman has a type 1 TZ (entirely visible and only ectocervical), orThe woman has a type 2 TZ (entirely visible and has an endocervical component), where the probe tip will achieve complete ablation of the SCJ epithelium, that is, where it can reach the upper limit of the TZ.

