**Figure 3 F3:**
[figure not shown]
Protocol for management of HPV positive women. HPV, human papillomavirus.

Those not eligible for thermal ablation will be referred to a gynaecologist for colposcopy, followed by biopsy or LEEP (loop electrosurgical excision procedure) as clinically indicated, at the same visit where possible. Cancer cases suspected at VAT or at colposcopy will be referred to local referral hospitals.

Those positive for less carcinogenic Group 1d HPV types (39, 51, 56, 59) ±35 will be offered triaging with VIA (figure 3). VIA positive women will be assessed for ablative treatment and offered the same, if eligible. VIA-positive women not eligible for ablation will be referred for colposcopy, followed by biopsy or LEEP as clinically indicated. VIA-negative women will be asked to return for a repeat HPV test in 12 months to assess clearance. Those with persistent Group 1d HPV (±HPV 35) infections will be offered colposcopy, followed by biopsy or LEEP as clinically indicated. Women with new positivity for Group 1a-c HPV types will be offered ablative treatment (following VAT), if eligible, or if ineligible, referred for further assessment at colposcopy.

Those who undergo any ablative treatment (VAT or post-VIA) will be offered a follow-up HPV test in 12 months.

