#### Confirmation of underlying disease

All consenting HPV positive women requiring treatment will undergo biopsy before treatment, to confirm disease burden, positive predictive value of the tests and identify occult cancers. Biopsies will be transported in formalin to the pathology laboratory of the Christian Medical College Vellore or the Zoram Medical College. No biopsies will be taken from screen negative women, as determining sensitivity of the screening test is not an objective of this study, with these parameters well studied in multiple trials.

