#### Training

Medical officers are being trained for management of screen positive women using thermal ablation, VAT and VIA triage, while gynaecologists are additionally being trained for colposcopy and LEEP. Other training includes training of nurses, social workers, community level workers, lab technicians, data entry operators and programme managers for various aspects such as community mobilisation, health education, counselling for follow-up, data management and laboratory processes.

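### The ablation criteria join the endocervical limit and the 75% size limit with *or*, so read literally the size limit excludes no ectocervical lesion

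*Protocol article*

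**What the plan says.** Under Management of screen positive women, the Protocol article lists the criteria for thermocoagulation. The first item asks for a TZ that can be seen in full and a lesion that is entirely in view and raises no suspicion of cancer. It then adds that the lesion "does not extend into the endocervix, or the lesion does not occupy more than 75% (3 quadrants) of the TZ".

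The next two items concern TZ type. One is "The woman has a type 1 TZ (entirely visible and only ectocervical"). The other is a type 2 TZ for which the probe achieves complete ablation, explained as "where it can reach the upper limit of the TZ".

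The text after Figure 3 in the same section gives the consequence of failing the criteria: "Those not eligible for thermal ablation will be referred to a gynaecologist for colposcopy". The same holds on the triage route: "VIA-positive women not eligible for ablation will be referred for colposcopy". Suspected cancer is handled separately: "Cancer cases suspected at VAT or at colposcopy will be referred to local referral hospitals".

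**The concern.** This rule separates ablation from colposcopy with biopsy or LEEP. If *or* is taken at its word, a woman whose lesion exceeds a limit that the protocol itself states would be ablated rather than referred.

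The Training section says that "Medical officers are being trained for management of screen positive women using thermal ablation, VAT and VIA triage". Care is spread over several sites and two state health systems, so the criteria need to have one reading. According to Ethics and dissemination, recruitment began on 21 March 2025 and is expected to finish by June 2026, so a correction may still reach women awaiting management.

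There is also a smaller reporting effect. In Table 3, referral compliance is calculated among women referred because they could not be ablated. If sites read the rule differently, that denominator would mean different things at different sites.

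**Working it through.** No sample size, power or event count is involved. The check is on the logic of the rule.

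**Inputs, all from Management of screen positive women**

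- A: TZ fully visible
- B: lesion wholly visible
- C: lesion not suspicious
- D: lesion does not reach the endocervix
- E: lesion covers 75% of the TZ or less
- T: TZ is type 1, or type 2 and reachable by the probe

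**Step 1: parsing the sentence.** Had one negation governed both limits (neither reaching the endocervix nor exceeding 75%), both would apply. Here the subject and the negation are stated again after *or*, so either limit suffices. The natural reading is A and B and C and (D or E). The only other literal reading is (A and B and C and D) or E. With A, B and C met, the two readings agree:

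| D (not endocervical) | E (≤75%) | Either literal reading | All joined by *and* |
|---|---|---|---|
| yes | yes | eligible | eligible |
| yes | no | eligible | not eligible |
| no | yes | eligible | not eligible |
| no | no | not eligible | not eligible |

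The second row is the main problem: an ectocervical lesion over 75% passes. Under the second reading matters are worse, because a lesion of 75% or less would pass this item even if it were suspicious or not fully seen.

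**Step 2: adding the TZ-type items.** Hold A, B and C as met and take T as also required. The combinations are 3 TZ classes × 2 (endocervical or not) × 2 (over 75% or not) = 12. A type 1 TZ is purely ectocervical, so its 2 endocervical cells drop out: 12 − 2 = 10. T is met in 2 (type 1) + 4 (reachable type 2) = 6 of them:

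| TZ | Endocervical | Size | *and* | *or* |
|---|---|---|---|---|
| type 1 | no | ≤75% | eligible | eligible |
| type 1 | no | >75% | no | **eligible** |
| type 2, reachable | no | ≤75% | eligible | eligible |
| type 2, reachable | no | >75% | no | **eligible** |
| type 2, reachable | yes | ≤75% | no | **eligible** |
| type 2, reachable | yes | >75% | no | no |

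The 4 cells with an unreachable type 2 TZ fail T under either wording.

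- Joined by *and*: 2 eligible, so the limits exclude 6 − 2 = 4.
- Joined by *or*: 5 eligible, so the limits exclude 6 − 5 = 1.
- Extra eligible cells: 5 − 2 = 3. Two are ectocervical lesions over 75%; one is an endocervical lesion of 75% or less in a reachable type 2 TZ.

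**Step 3: looking for a repair elsewhere.** The TZ items set no size limit, and the 75% figure appears nowhere else in the text shown. Both referral sentences after Figure 3 apply only to women already judged ineligible, so they inherit the rule and do not correct it.

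**Step 4: frequency.** The article does not give the Group 1a–c share of positives, VIA positivity or lesion sizes. The number of women in the three extra cells cannot be calculated.

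**The case against.** The strongest reply is that this is a slip of drafting. Nobody writes a 75% cap intending it to have no effect, and a clinician trained in visual assessment would probably apply both limits. The criteria cite a guideline, Figure 3 is not visible here, and training materials may already be worded correctly. Nothing shows that staff work from this sentence. There are also safeguards: "All consenting HPV positive women requiring treatment will undergo biopsy before treatment", and an HPV test is offered 12 months after ablation. Table 3 counts referrals actually made, so it can be calculated as written and would shift only if clinicians really used the *or* reading. The list layout may have been lost in text extraction, so the cell counts rest on an assumed joining of the items.

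Much of this stands, and it limits the weight of the point. Both limits were probably meant, and harm depends on the wording being followed. It does not remove the error. The article states the operative criteria outright, so this is not detail left to another document. The biopsy covers consenting women only, and the text does not say that ablation waits for histology; the 12-month test comes after treatment. The central result does not depend on the list layout either: a type 1 TZ with an ectocervical lesion over 75% satisfies both the first item as written and the TZ item, so it is eligible however the items are joined.

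**Conclusion.** The concern holds. As written, the 75% limit excludes no fully seen, non-suspicious ectocervical lesion from ablation. With an acceptable TZ, the two limits together exclude one logical combination of six instead of four. The count assumes that the TZ-type item is required alongside the first item; the finding about large ectocervical lesions in a type 1 TZ does not need that assumption. That *and* was intended is an inference, since the cited guideline was not consulted.

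This should be fixed because it governs treatment. It does not threaten the trial's inference: the management pathway is common to both arms, so the between-arm comparison and the power are essentially unaffected. Suspected cancers are not at issue, since they have their own referral route.

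**What to change.** After checking the guideline cited at that sentence, restate the rule with every connective explicit: TZ fully visible AND any lesion wholly visible AND not suspicious AND not reaching the endocervix AND covering no more than 75% of the TZ, AND (type 1 TZ OR type 2 TZ whose upper limit the probe can reach). Use the same wording in site training and the registry, and when classifying women as ineligible for ablation for Table 3. Ask each site to confirm that it applies both limits, and review visual-assessment records only where a site does not. If one limit really is meant as an alternative, say so and give the reason.

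The cost is one conjunction, one joining phrase, matching wording in training and registry, and one query per site. Sample size and power do not change. The possible downside is slightly more colposcopy referrals, which is a burden where road access is poor.

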**Figure 3 F3:**
[figure not shown]
Protocol for management of HPV positive women. HPV, human papillomavirus.

Those not eligible for thermal ablation will be referred to a gynaecologist for colposcopy, followed by biopsy or LEEP (loop electrosurgical excision procedure) as clinically indicated, at the same visit where possible. Cancer cases suspected at VAT or at colposcopy will be referred to local referral hospitals.

Those positive for less carcinogenic Group 1d HPV types (39, 51, 56, 59) ±35 will be offered triaging with VIA (figure 3). VIA positive women will be assessed for ablative treatment and offered the same, if eligible. VIA-positive women not eligible for ablation will be referred for colposcopy, followed by biopsy or LEEP as clinically indicated. VIA-negative women will be asked to return for a repeat HPV test in 12 months to assess clearance. Those with persistent Group 1d HPV (±HPV 35) infections will be offered colposcopy, followed by biopsy or LEEP as clinically indicated. Women with new positivity for Group 1a-c HPV types will be offered ablative treatment (following VAT), if eligible, or if ineligible, referred for further assessment at colposcopy.

Those who undergo any ablative treatment (VAT or post-VIA) will be offered a follow-up HPV test in 12 months.

#### Confirmation of underlying disease

All consenting HPV positive women requiring treatment will undergo biopsy before treatment, to confirm disease burden, positive predictive value of the tests and identify occult cancers. Biopsies will be transported in formalin to the pathology laboratory of the Christian Medical College Vellore or the Zoram Medical College. No biopsies will be taken from screen negative women, as determining sensitivity of the screening test is not an objective of this study, with these parameters well studied in multiple trials.

#### Training

Medical officers are being trained for management of screen positive women using thermal ablation, VAT and VIA triage, while gynaecologists are additionally being trained for colposcopy and LEEP. Other training includes training of nurses, social workers, community level workers, lab technicians, data entry operators and programme managers for various aspects such as community mobilisation, health education, counselling for follow-up, data management and laboratory processes.

#### Concomitant screening

Among those who undergo HPV screening at a facility, concomitant VIA, if performed based on the woman’s request, will be noted.

### Outcomes

The trial is a type 3 hybrid implementation research trial, which will primarily compare implementation outcomes while collecting data on clinical outcomes.^27^ Evaluation of the trial will use a mixed methods approach. The primary outcome will be the percentage of well-managed women, among all eligible women aged 30–49 years, measured 3 months from the last date of recruitment. Well-managed refers to having been screened using HPV testing and undergoing further assessment and treatment, based on results. Later analyses after the trial period will summarise long-term follow-up, including compliance with repeat HPV testing at 12 months. All quantitative implementation and effectiveness outcomes are outlined in tables3^5^.

**Table 3 T3:** Quantitative outcome indicators at the individual level

Outcome	Indicator*	Formula for calculation
Primary outcome: Overall effectiveness of the programme	Percentage well managed (screened and managed appropriately) out of all eligible women in study area	Number of women who received appropriate assessment or treatment based on HPV results/total number of eligible women in study area
Screening coverage (reach)	Percentage of women screened with HPV testing among eligible women	Number of women screened with HPV testing/total number of eligible women in study area
Initial follow-up visit compliance	Percentage of HPV positive women who attend the first follow-up assessment	Number of HPV positive women who reported to a follow-up clinic/HPV positive women
Referral visit treatment compliance among those ineligible for ablation	Percentage of HPV positive women who attend a higher centre among those referred based on the initial follow-up assessment	Number of HPV positive women who underwent LEEP or appropriate management/HPV positive women who were referred to a higher centre based on ineligibility for ablation
Treatment rate (programme effectiveness in providing treatment)	Percentage of women treated among those HPV positive eligible for treatment	Number of HPV positive women who were treated/women who were eligible for treatment
12 month follow-up compliance	Percentage of women who complete repeat HPV testing at 12 months among women due for a 12 month follow-up HPV test	Number of women who complete a 12 month repeat HPV test/(number treated at baseline based on presence of highest risk genotypes or VIA positivity with other high risk genotypes+women with other high risk genotypes and negative VIA at baseline)
Acceptability	Percentage of screened women who would be willing to repeat self-collection or who would be willing to recommend the test to other women	Number who would be willing to repeat the test or would recommend the test/interviewed women who have completed screening
	Satisfaction rating for self-collection	Mean satisfaction score out of 5
	Percentage of women who underwent diagnostic or therapeutic procedures who experienced side effects leading to hospital visits	Number of screened positive women who reported side effects requiring hospital visits/number of screen positive women who underwent follow-up assessment

* Sources of information: screening registry for rates of screening and treatment; sample surveys for acceptability indicators.

HPV, human papillomavirus; LEEP, loop electrosurgical excision procedure; VIA, visual inspection of the cervix with acetic acid.

**Table 4 T4:** Quantitative outcomes relating to health systems and settings

Outcome	Indicator	Formula for calculation	Means of verification
Adoption by providers and setting	Percentage of clusters that offered planned interventions	Number of clusters in which self-collection was offered to eligible women/clusters randomised to the specific arm	Programme records/study staff
Implementation fidelity for self-collection	Proportion of HPV testing that was done as self-collection	Number of women that performed self-collection/number of women screened using HPV testing	Screening registry
Implementation fidelity for approach to programme	Proportion of clusters in each arm that offered self-collection according to protocol	Number of clusters that offered screening in community or facility based on allocation/number of clusters in the arm	Programme records
Sustainability	Perceived sustainability of the programme approaches	The Intervention Scalability Assessment tool	Final stakeholder workshop

HPV, human papillomavirus.

**Table 5 T5:** Additional quantitative process indicators

Process indicator	Indicator explanation	Formula or indicator for calculation	Means of verification
Invitation	Percentage of women aged 30–49 years who received information about screening among eligible women	Number of women aged 30–49 years who received information about HPV testing/total number of women aged 30–49 years	Sample survey at the end of the study period
Education session coverage	Percentage of clusters that offered at least one community-based educational programme and an appropriate number of small group sessions in each arm	Number of clusters that offered at least one community-based educational programme and an appropriate number of small group sessions (at least one session for every 50 women)/total study clusters per arm	Programme records
	Number of educational sessions organised in 12 months in each cluster	Mean number of sessions in each arm	
HPV sample adequacy	Adequacy of DNA samples received for testing	Number of inadequate samples received/total number of samples received	Screening registry
Implementation costs and cost effectiveness	Costs of invitation, obtaining samples, transport, laboratory testing, treatment, data management	Cost per woman screened and cost per HPV positive case treated	Micro-costing exercise

HPV, human papillomavirus.

We will also capture the quantity and costs of programme resources used in both arms, including costs of equipment, consumables, labour, transport, screening registry, educational materials and treatment of precancer. These costs will inform future cost-effectiveness analysis by comparing costs and effects of self-collection with VIA screening. Feedback surveys, including data on acceptability and possible harms, will be conducted among all consenting screen positive women and a random sample (10%, simple random sampling) of screen negative women from each site. Barriers and facilitators for providers and target women will be based on qualitative studies using the methodology described earlier.^22^ Focus group discussions (FGDs) with CHWs, key informant interviews with programme staff and interviews/FGDs with unscreened women and community members, including men, will be conducted to understand factors affecting implementation, challenges with screening and follow-up, as well as suggestions for future programmes. A final stakeholder workshop will be held to discuss trial findings and to assess sustainability using the Intervention Scalability Assessment tool.^41^

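### Table 3's side-effects formula divides survey reports by all assessed screen-positive women, not by interviewed women who had a procedure, so it can understate the rate

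*Protocol article*

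**What the plan says.** The side-effects row is the last entry in the Acceptability block of Table 3 (protocol article, Outcomes). The indicator is worded as "Percentage of women who underwent diagnostic or therapeutic procedures who experienced side effects leading to hospital visits". The formula beside it is "Number of screened positive women who reported side effects requiring hospital visits/number of screen positive women who underwent follow-up assessment".

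The table's footnote gives the data sources: "screening registry for rates of screening and treatment; sample surveys for acceptability indicators". The text after Table 5 adds: "Feedback surveys, including data on acceptability and possible harms, will be conducted among all consenting screen positive women". Screen-negative women are sampled at 10%; screen-positive women are not sampled.

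The first row of the same block has a denominator limited to respondents: "Number who would be willing to repeat the test or would recommend the test/interviewed women who have completed screening".

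**The concern.** Two mismatches sit in one table cell.

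- **Population.** The indicator concerns women who had a procedure, while the formula counts every screen-positive woman who attended assessment. Under the article's own pathway these may be different groups.
- **Source.** The numerator can only come from women who answered the survey, but the denominator is not limited to them. Non-response is therefore scored as no side effect.

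Both mismatches act in the same direction under simple assumptions: they lower the reported rate. This is the only row in Tables 3 to 5 that expresses harm as a rate, so it is the figure that someone planning a programme would read. With the formula as written, a low survey response would look like good tolerability.

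**Working it through.** **Is there a figure to reproduce?** No. The article states no expected side-effect rate, survey response or procedure share for this row. The check is therefore a comparison of definitions followed by algebra on assumed values.

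**Step 1: who is in the denominator.** Under Management of screen positive women, women with a Group 1a–c type are offered VAT: "VAT involves examination for eligibility for treatment using 3%–5% acetic acid application". For the other group: "Those positive for less carcinogenic Group 1d HPV types (39, 51, 56, 59) ±35 will be offered triaging with VIA". Those who are negative at that step receive no treatment at baseline: "VIA-negative women will be asked to return for a repeat HPV test in 12 months to assess clearance". The section on confirmation of underlying disease reserves pre-treatment biopsy for consenting women who need treatment. An assessed, VIA-negative woman is thus in the denominator without biopsy, ablation, colposcopy or LEEP at baseline. Whether she had a diagnostic procedure depends on whether VIA counts as one, and the article does not say.

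**Step 2: who can be in the numerator.** Only women who consented to the survey and answered it.

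**Step 3: formula.** Let

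- s = share of assessed women who answer the survey,
- f = share of assessed women who had a procedure,
- r_p = side-effect risk with a procedure,
- r_0 = side-effect risk without one.

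If response is unrelated to harm, and only assessed women enter the numerator, the Table 3 formula returns s × [f × r_p + (1 − f) × r_0]. The indicator as described is r_p. With r_0 = 0 the ratio of the two is s × f.

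**Step 4: numbers.** The values of s and f, and the true rate of 10%, are assumptions chosen to show the range.

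| s | f | ratio s × f | reported if the true rate is 10% |
|---|---|---|---|
| 1.0 | 1.0 | 1.00 | 10% |
| 0.9 | 1.0 | 0.90 | 9% |
| 1.0 | 0.8 | 0.80 | 8% |
| 0.9 | 0.8 | 0.72 | 7.2% |
| 0.8 | 0.8 | 0.64 | 6.4% |
| 0.7 | 0.6 | 0.42 | 4.2% |

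If VAT and VIA count as procedures, f = 1 and the ratio is s alone, which is 0.7 to 1.0 over the same assumed range.

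**Step 5: what restriction to respondents does.** With numerator and denominator both limited to interviewed women who had a procedure, the ratio is 1 under the same assumptions. It is not 1 if harmed women answer more often. As an illustration with f = 1 and a true rate of 10%, let 90% of harmed and 70% of unharmed women respond. The formula as written gives 0.10 × 0.90 = 9.0%. The respondent-only rate is 0.09 / (0.09 + 0.90 × 0.70) = 0.09 / 0.72 = 12.5%.

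**Scale.** The Discussion expects fewer than 10% of women to be HPV positive. If all 2912 women in the sample size were screened, that is at most about 2912 × 0.10 = 291 screen-positive women in both arms together.

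**The case against.** The strongest reply is that the two descriptions may name the same women. Every assessed woman has VAT or VIA, and either could be called a diagnostic procedure. On that reading nobody in the denominator lacks a procedure and the dilution disappears. This stands as a possible reading. It does not remove the non-response problem, and it would make the indicator's restriction to women with procedures redundant.

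Second, a reader might take the footnote's reference to sample surveys to mean that only some screen-positive women are approached. The article does not support that: all consenting screen-positive women are surveyed. Those missing are non-consenters and non-responders, and their share is unknown and could be small.

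Third, a reader might infer that the rate is certain to be too low. It is not. The bias is zero if all assessed women respond and VAT/VIA counts. The numerator is also not explicitly tied to assessed women or to effects of a procedure, which could push the rate slightly the other way.

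Fourth, it is tempting to say that harm would otherwise go unrecorded, or that the bias would differ by arm. Neither is supported. The section on study governance has a Steering Committee monitoring adverse events, and explains the absence of a separate safety committee by the identical screening and treatment practices in both arms. Nothing in the article suggests that survey response among screen-positive women would differ by arm.

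Finally, a condensed article may leave operational definitions to a fuller document. That would excuse silence, but here a formula is stated and it does not match its own indicator.

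**Conclusion.** The point holds in a limited form. Followed as written, the formula gives a side-effect rate that is too low whenever some assessed women do not answer the survey and response is unrelated to harm. It is lower still if VAT or VIA alone is not a procedure. The size runs from no bias to 0.42 of the true rate over the assumed range. It rests on s and f, which the article does not give, on independence of response and harm, and on negligible side effects in women without a procedure. The definitional mismatch itself rests on no assumption about rates. Severity is low: this is one secondary row in an acceptability block, and it touches neither the primary outcome nor the sample size.

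**What to change.** Change the Table 3 row in three ways.

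1. State which procedures count. Colposcopy belongs on the list with biopsy, ablation and LEEP, and the row should say explicitly whether VAT or VIA alone counts.
2. Restrict both numerator and denominator to interviewed screen-positive women who had such a procedure, in line with the interviewed-women denominator of the first acceptability row.
3. Report survey response among eligible women by arm beside the rate.

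The cost is one table cell and one extra reported figure. The registry is described as recording follow-up assessments and treatment of precancer; whether it also identifies biopsy and colposcopy, and whether interview status can be linked to it, is not stated and should be confirmed. The denominator becomes somewhat smaller, so the estimate is slightly less precise. The respondent-only rate may be too high if women with side effects are likelier to answer, which is why the response figure should accompany it. Recruitment is expected to finish by June 2026 (Ethics and dissemination), so the wording can be settled before analysis.

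### The acceptability survey over-samples screen-positive women ten to one, but Table 3 computes willingness and satisfaction among screened women without weights

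*Protocol article*

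**What the plan says.** All references are to the Protocol article.

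- **Sampling (Outcomes, text after Table 5).** The feedback surveys, which cover harms as well as acceptability, "will be conducted among all consenting screen positive women and a random sample (10%, simple random sampling) of screen negative women from each site".
- **Target (Table 3, Acceptability).** The indicator is the "Percentage of screened women who would be willing to repeat self-collection or who would be willing to recommend the test to other women".
- **Formula (Table 3, same row).** "Number who would be willing to repeat the test or would recommend the test/interviewed women who have completed screening".
- **Satisfaction (Table 3, next row).** "Mean satisfaction score out of 5".
- **Source (footnote to Table 3).** The registry supplies screening and treatment rates; the footnote gives "sample surveys for acceptability indicators".
- **Use (Statistical analysis).** Acceptability is listed among the outcomes whose differences are to be estimated at the individual level.
- **Expected positivity (Discussion).** Fewer than 10% of women are expected to be HPV positive.

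Nowhere does the article mention survey weights, standardisation or reporting of acceptability by HPV result.

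**The concern.** The label and the formula describe different populations. The label refers to everyone screened, nearly all of whom should be HPV negative. The formula averages over respondents drawn at 100% from one result group and at 10% from the other, so positives count about ten times more than their place among screened women warrants.

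This matters if positives and negatives answer differently, which is plausible. A negative result arrives as a message. A positive result brings a home visit, counselling and referral, and for some women examination, biopsy or ablation. Acceptability is a declared secondary outcome of a trial meant to inform state and national programmes, so a percentage that does not estimate what its label says could be misread.

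**Working it through.** The article gives no expected value or sample size for the survey, so there is no planned figure to reproduce. The check is a direct calculation.

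**Inputs from the article:** sampling fraction 1 for consenting positives; f = 0.10 for negatives; positivity p below 10%.

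**Assumptions:** p from 3% to 10%, since no point value is given; full response unless stated; acceptability A_pos and A_neg by result, since the article gives neither.

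**Formulas**

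- Share of positives among respondents: s = p / (p + f(1 − p)).
- Printed formula: s·A_pos + (1 − s)·A_neg.
- Percentage among screened women: p·A_pos + (1 − p)·A_neg.
- Error of the printed formula: (s − p)(A_pos − A_neg).
- Kish design effect with weights 1 and 10, per screened woman: [p + f(1 − p)]·[p + 10(1 − p)], because the weights sum to 1. Interval width grows by its square root.

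Example at p = 10%: s = 0.10 / (0.10 + 0.09) = 0.526; design effect = 0.19 × 9.1 = 1.73; square root 1.31.

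| p | s | s − p (points) | Error, 10-point gap | Error, 20-point gap | Design effect | Wider interval |
|---|---|---|---|---|---|---|
| 3% | 23.6% | 20.6 | 2.1 | 4.1 | 1.24 | 11% |
| 5% | 34.5% | 29.5 | 2.9 | 5.9 | 1.38 | 18% |
| 7% | 42.9% | 35.9 | 3.6 | 7.2 | 1.53 | 24% |
| 10% | 52.6% | 42.6 | 4.3 | 8.5 | 1.73 | 31% |

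With no gap the error is zero in every row. The sign follows the gap: the printed figure is too low if positives are less favourable and too high if they are more favourable. For instance, 95% in negatives and 85% in positives at p = 5% gives 94.5% among screened women, against 91.6% from the formula.

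**Consent.** If 60% of positives consent and every sampled negative responds (assumed), s is 0.06 / (0.06 + 0.09) = 40% at p = 10%, and 0.03 / (0.03 + 0.095) = 24% at p = 5%. The imbalance shrinks but remains.

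**Number screened.** It cancels out of s. For scale only, if the 40% and 52% well-managed assumptions stand in for the share screened of 1456 women per arm, p = 10% gives about 58 positives with 52 sampled negatives, or 76 with 68.

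**Arm contrast (illustrations)**

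- A 10-point arm effect confined to negatives is 10 × (1 − p) among screened women and 10 × (1 − s) in the printed figure: 9.0 against 4.7 points at p = 10%, and 9.5 against 6.6 at p = 5%.
- With 95% in negatives and 80% in positives in both arms, but positivity 5% in one and 8% in the other, s is 34.5% and 46.5%. The printed difference is 1.8 points; among screened women it is 0.03 × 15 = 0.45.

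**The case against.** The strongest reply is that Table 3 is a dictionary of indicators. Most of its rows are simple ratios and none mentions clustering, although the Statistical analysis section adjusts for it. On that view the table says who is counted, and weighting belongs in the analysis plan. The row also names interviewed women as its denominator and the footnote calls the source a sample survey, so nothing is hidden. This does not dispose of the point: the article itself fixes the target, the sampling fractions and the formula, and taken literally the three do not agree.

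Other parts of the reply stand. Taking every positive is a sound choice, because the same survey collects harms, and the side-effects row is restricted to screen-positive women and so is unaffected. The primary outcome is untouched. Acceptability is one of several secondary outcomes and is also studied qualitatively.

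A reader might infer more than the documents support:

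- **That the figure would mostly reflect positive women who had procedures.** Positives are a majority of respondents only near the 10% ceiling, and being surveyed does not depend on having attended follow-up or been treated.
- **That a particular bias is established.** Its size and direction depend wholly on an acceptability gap that the documents do not give, and zero is possible.
- **That the arm comparison is necessarily biased.** Both arms use the same sampling fractions. Distortion requires positivity or consent to differ between arms, or the arm effect to differ by HPV result.

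**Conclusion.** The point holds as a mismatch between a stated target and a stated formula. Given the sampling fractions, full response and positivity of 3 to 10%, positives are about a quarter to a half of respondents; that part needs no assumption about attitudes. The resulting error is conditional: 0 points with no gap, about 2 to 4 with an assumed 10-point gap, and about 4 to 8.5 with an assumed 20-point gap. The same reasoning applies to mean satisfaction, with the gap measured on its 5-point scale. The consequence is confined to a secondary outcome and should be corrected before analysis; it does not threaten the trial's main conclusion.

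**What to change.** Keep the sampling as it is. In Table 3, define willingness and mean satisfaction for screened women with inverse sampling-fraction weights (1 for positives, 10 for negatives), adjusted for non-response within site and arm. Use the weighted figures for the arm comparison, and also report positives and negatives separately in each arm.

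The survey is already drawn by site and HPV result, and arm follows from cluster allocation, so no extra interviews are needed. Some adjustment cells will be small: with 40% screened as the stand-in and positivity of 3 to 5%, an arm has only about 17 to 29 positives across all sites, so the plan should allow cells to be combined.

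The cost is precision. The design effect of about 1.24 to 1.73 makes intervals for the weighted overall figure roughly 11 to 31% wider than an equally weighted sample of the same size would give. The separate results by HPV status do not carry that penalty.
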